## Abstract

**Background:**

Many patients with type 2 diabetes fail to achieve good glycaemic control. Poor control is associated with complications including coronary heart disease (CHD). Effective self-management and engagement in health behaviours can reduce risks of complications. However, patients often struggle to adopt and maintain these behaviours. Self-management interventions have been found to be effective in improving glycaemic control. Recent developments in the field of genetics mean that patients can be given personalised information about genetic- and lifestyle-associated risk of developing CHD. Such information may increase patients’ motivation to engage in self-management. The Coronary Risk in Diabetes (CoRDia) trial will compare the effectiveness of a self-management intervention, with and without provision of personalised genetic- and lifestyle-associated risk information, with usual care, on clinical and behavioural outcomes, the cognitive predictors of behaviour, and psychological wellbeing.

**Methods/Design:**

Participants will be adults aged 25–74 years registered with general practices in the East of England, diagnosed with type 2 diabetes, with no history of heart disease, and with a glycated haemoglobin level of ≥6.45 % (47 mmol/mol). Consenting participants will be randomised to one of three arms: usual care control, group self-management only, group self-management plus personalised genetic- and lifestyle-associated risk information. The self-management groups will receive four weekly 2-hour group sessions, focusing on knowledge and information sharing, problem solving, goal setting and action planning to promote medication adherence, healthy eating, and physical activity. Primary outcomes are glycaemic control and CHD risk. Clinical data will be collected from GP records, including HbA1c, weight, body mass index, blood pressure, and HDL and total cholesterol. Self-reported health behaviours, including medication adherence, healthy eating and physical activity, and cognitive outcomes will be assessed by questionnaire. Measures will be taken at baseline, 3 months (questionnaire only), 6 months and 12 months post-baseline.

**Discussion:**

This study will determine whether the addition of personalised genetic- and lifestyle-associated CHD risk information to a group self-management intervention improves diabetes control and CHD risk compared with group self-management and usual care. Effectiveness of the combined intervention on health behaviours cognitions theorised to predict them, and psychological outcomes will also be investigated.

**Trial registration:**

This study has been registered at ClinicalTrials.gov; registration identifier NCT01891786, registered 28 June 2013.

**Electronic supplementary material:**

The online version of this article (doi:10.1186/s13063-015-1073-7) contains supplementary material, which is available to authorized users.

## Background

Approximately 2.3 million people in the UK aged over 17 years have diagnosed diabetes, of which 90 % are diagnosed with type 2 [1]. This number is expected to rise to 4 million by 2025 [2]. Complications in diabetes arise from poor glycaemic control [3], and include renal disease, retinopathy, and peripheral vascular disease [1]. People with diabetes have two times the risk of developing coronary heart disease (CHD) compared with the general population [1], and CHD is the cause of death in 52 % of people with diabetes [4]. Good glycaemic control has, however, been found to be associated with reductions in the complications associated with diabetes and the risk of developing CHD [3].

Glycaemic control and the health risks associated with diabetes can be managed through appropriate self-management behaviours including taking medication appropriately, regular physical activity, following a healthy diet and checking feet. These behaviours are also established as important in the prevention of CHD risk in people with and without diabetes. Therefore, interventions to increase adherence to these behaviours in patients with type 2 diabetes will have the dual benefit of reducing both the risk of diabetes complications and CHD.

Many people with diabetes experience difficulties in consistently carrying out the recommended behaviours. To support patients with diabetes to achieve better glycaemic control, the Quality and Outcomes Framework (QOF) recommends that all patients with diabetes are referred to group educational intervention within 9 months of diagnosis [5]. In recognition that the provision of information is insufficient to achieve the required behaviour change, self-management interventions (SMIs) have been developed and recognised as a key part of the delivery of care for people with diabetes by the National Institute for Health and Care Excellence (NICE) [6, 7].

SMIs for people with diabetes have been widely implemented both in the UK and elsewhere. Systematic and meta-analytic reviews indicate that they are effective in improving glycaemic control (glycated haemoglobin (HbA1c) [8, 9]). However, few studies have investigated the effect of SMIs on other indicators of CHD risk, with the exception of body mass index (BMI) [9]. A review of systematic reviews of diabetes SMIs found that fewer than half of included studies investigated outcomes associated with CHD risk, such as blood pressure and lipid profile [10], thus investigation of intervention effects on clinical risk factors associated with CHD is warranted.

Reviews of the effect of SMIs for diabetes have indicated that the most effective interventions are those that target specific disease prevention behaviours such as healthy eating and physical activity [9], and those that use theory to specify the intervention components [11]. A systematic review has indicated that interventions employing techniques from social learning theory (SLT) [12, 13] such as modelling, increasing self-efficacy and skills rehearsal were most effective for changing health behaviours [11]. The University College London Diabetes Self-Management Programme (UCL-DSMP) [14] is one such programme, based on SLT and employing these techniques. Compared with standard care, this intervention resulted in greater positive change in dietary behaviours and physical activity, and showed a trend towards significance in predicting greater improvements in HbA1c after 3 months.

Evaluations of SMI interventions can be enhanced by the measurement of their effects on the cognitive predictors of health behaviour, described in theories of behaviour. Investigating the effect of an intervention on cognitions can provide an explanation of intervention effects or null findings [15]. The Health Action Process Approach (HAPA) [16] integrates several theories describing the predictors of health behaviour, and states behavioural intention or motivation is a key determinant of it. Antecedents of intention include perceived risks, self-efficacy to perform, and expectancies about the outcomes of the behaviour. Planning, social support, and maintenance and recovery self-efficacy are specified as post-intentional cognitions that predict behaviour. The HAPA has been found to explain variance in intentions and behaviour for several behaviours including healthy eating in a healthy population [17], and physical activity in patients with heart failure [18].

### Motivating engagement in self-management interventions: personalised risk estimates

Increasing motivation to engage in and maintain self-management behaviours may be one way to increase the effect of SMIs on glycaemic control and engagement in healthy behaviours. Current QOF guidance requires that patients receive information about their lifestyle-associated risk of CHD annually, using standardised risk calculators e.g. the UK Prospective Diabetes Study (UKPDS) [19]. It has been put forward that the salience of this information about this modifiable risk may be increased by providing it alongside information about unmodifiable genetic risk of developing CHD [20].

Recent developments in the field of genetics have provided the opportunity to investigate the behavioural and clinical effect of providing a personalised estimate of both genetic- and lifestyle-associated risk of CHD. A CHD genetic risk score based on 19 CHD risk loci has been evaluated and found to have potential clinical utility in addition to conventional risk factors in a group of UK middle-aged healthy men [21]. This genetic risk score can then be combined with a conventional risk score from lifestyle risk calculators to give an overall estimate of 10-year CHD risk.

Currently there is no evidence to suggest individuals will perceive engaging in risk-reducing behaviours to be less beneficial should they receive a high risk result [22], and evidence indicates that participants are not likely to perceive genetics to be the sole cause of illness [23]. However, there is limited evidence that provision of personalised risk information alone will effect behaviour change where support to change behaviour is not provided. A Cochrane Review [24] has identified a small number of clinical trials in which behavioural effects of genetic risk information have been examined, and found no effect of receiving a test result on smoking cessation, physical activity, taking medication and vitamin use. An effect on dietary changes was found in only one study. The review also found that while they aimed to change behaviour, these studies did not report the use of additional behaviour change techniques such as goal setting or coping planning. However, there is some evidence for an effect of receiving a genetic risk result on the cognitions that predict behaviour; an effect of receiving a test result on smoking cessation intentions was found for analogue studies in which behavioural outcomes were not investigated due to the absence of an available test. Furthermore, receiving a risk result has been found to predict change in other cognitions theorised to predict behaviour in clinical and analogue studies, including fear arousal, perceptions of risk of developing disease, and perceived effectiveness of the target behaviour in reducing risk. Further intervention may therefore be required to help translate these cognitive changes into behaviour change. Together these findings underline the potential utility of investigating the behavioural and clinical effects of providing personalised genetic- and lifestyle-associated risk information in conjunction with an SMI.

### Study aims

The Coronary Risk in Diabetes study (CoRDia) aims to investigate the effect of an SMI with and without personalised genetic- and lifestyle-associated risk information, compared with usual care. The primary outcomes are glycaemic control measured as HbA1c, and percentage CHD risk assessed using the UKPDS risk calculator.

Secondary outcomes are other indicators of CHD risk including total and high-density lipoprotein (HDL) cholesterol, blood pressure, weight and BMI, and behaviours including adherence to medication, diet and physical activity. The effect of personalised risk information and the SMI on the theory-based cognitive predictors of behaviour, quality of life, psychological wellbeing, and emotional response to having a genetic test will also be examined.

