### Power calculation

A clinically important change in HbA1c level of 12.5 % (SD 15.5 %) was identified from a Health Technology Assessment of blood glucose monitoring devices [35] over a period of 18 months. This represents a reduction in HbA1c (%) from 8 to 7 or from 9 to 7.9. As the current study has a shorter follow-up, we base our sample size calculations on a conservative change that would be clinically achievable in this time frame: an HbA1c change of 6.25 % representing a reduction from an HbA1c (%) of 8 to 7.5 or from 9 to 8.44 (this represents a change from 63.9 mmol/ml to 59.9 mmol/ml; and 74.9 mmol/ml to 69.4 mmol/ml).

The expected 6.25 % change in HbA1c (SD = 15 %) represents an effect size of d = 0.40, a small to moderate effect size (d = 0.2 – small, 0.5 – medium and 0.8 – large effect); equivalent to effect size f = 0.2 in G*Power [36] calculated for repeated measures, between-subjects analysis of variance (ANOVA) analyses. Based on the current design (three groups, four measurement points), alpha = 0.05, power = 80 %, f = 0.20 and a correlation between measurement points of 0.70, G*Power indicates a total sample size of 192. With an expected attrition rate of 20 %, a sample size of 240 (80 per study arm) will be sought.

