#### Main analyses

Spearman’s or Pearson’s correlations will determine relationships between variables and chi-squared analyses will be used to compare rates data. For the main group differences and time-based analyses, data will be analysed using intention-to-treat principle and then repeated with per protocol subsamples, for sensitivity analyses. For the main continuous outcome measures (HbA1c and CHD risk data) and secondary outcomes 3 x 3 mixed analysis of covariance (ANCOVA) controlling for existing group differences on key process variables will be conducted for each outcome, with post hoc comparisons using Sidak’s correction. Should the data meet the criteria for multi-level modelling, these analyses will be conducted in lieu of ANCOVA.

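### Two unranked primary outcomes have no error control between them; if success on either counts, the false-positive rate exceeds 5 % (at most 9.75 %)

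*Protocol article*

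**What the plan says.** Study aims sets two primary outcomes side by side: "The primary outcomes are glycaemic control measured as HbA1c, and percentage CHD risk assessed using the UKPDS risk calculator". The Primary outcomes section repeats the pair, gives no order, and lists HbA1c among the inputs to the UKPDS score.

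Main analyses specifies a 3 x 3 mixed ANCOVA, or a multi-level model in its place, which "will be conducted for each outcome, with post hoc comparisons using" Sidak's correction. That is the only multiplicity rule in the article. It sits inside each outcome's post hoc comparisons. The section gives no significance level and does not say what counts as success.

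The Power calculation concerns HbA1c only: "we base our sample size calculations on a conservative change that would be clinically achievable in this time frame". It then states "The expected 6.25 % change in HbA1c (SD = 15 %) represents an effect size of d = 0.40" and uses "alpha = 0.05, power = 80 %, f = 0.20 and a correlation between measurement points of 0.70". The 0.05 is not divided between the outcomes. No effect size, SD or power is given for UKPDS risk.

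**The concern.** With two primaries, separate models and no link between them, a natural way to follow the plan is to test each at 5 % and call the trial positive if either test is significant. The error rate for the trial's main claim is then not the 5 % on which the sample size was calculated.

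Two further features make the point worth settling. First, a result on UKPDS risk alone would have full primary status although nothing was planned for its power. Second, HbA1c enters the UKPDS score, so a positive result on both is not two independent confirmations.

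**Working it through.** **Inputs.** From the Power calculation: alpha 0.05, power 80 %, f = 0.20, three groups (k = 3), four measurement points (m = 4), correlation between measurement points rho = 0.70, attrition 20 %. From Study aims: two primary outcomes. From Main analyses: a separate model per outcome, and Sidak on post hoc pairs. The correlation between the two outcomes is not given, so a range of 0 to 0.9 is assumed.

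**1. Reproducing the plan's figure.** For a between-groups effect in repeated-measures ANOVA, the noncentrality is lambda = f² × N × m / (1 + (m − 1) × rho).
- At N = 192: 0.04 × 192 × 4 / (1 + 3 × 0.70) = 30.72 / 3.1 = 9.91.
- With 2 and 189 degrees of freedom and alpha 0.05, power is 80.5 %.
- 192 / 0.8 = 240.

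The stated 192 and 240 are confirmed. They require the whole 0.05 to be spent on HbA1c.

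**2. Upper limit of the error across two outcomes.** If either result suffices, each is tested at 0.05 and the tests are independent: 1 − 0.95² = 0.0975, or 9.75 %.

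**3. Effect of dependence.** This was simulated under the null with three equal arms, large-sample statistics and at least 1,000,000 trials per correlation. Sidak uses 1 − 0.95^(1/3) = 0.01695 per pair. Because the three pairs share arms, this amounts to about 4.5 % per outcome.

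| Assumed correlation between outcomes | Overall group test, either outcome | Sidak-corrected pairs, either outcome |
|---|---|---|
| 0 | 9.75 % (exact) | 8.8 % |
| 0.2 | 9.7 % | 8.7 % |
| 0.5 | 9.1 % | 8.2 % |
| 0.7 | 8.4 % | 7.6 % |
| 0.9 | 7.1 % | 6.4 % |

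Every entry is above 5 %. Dependence lowers the error but does not bring it to 5 % anywhere in this range.

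**4. The other success rule.** If both outcomes had to be significant, the chance that both are falsely significant cannot exceed that of either one alone, which is 5 %.

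**5. Ways to restore 5 %.**
- *Fixed sequence, HbA1c first.* If neither outcome truly differs, a false claim needs a false HbA1c result, so the error is 5 %. If only HbA1c truly differs, the sole possible false claim is on UKPDS risk, again at 5 % or less. The HbA1c test stays at 0.05, so its planned power stays at 80.5 % with 192 completers.
- *Splitting alpha, 0.025 each.* HbA1c power at 192 completers falls from 80.5 % to 71.8 %. The required N rises from 192 to 228, or 228 / 0.8 = 285 after attrition.

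**The case against.** The strongest reply is that the inflation rests on two premises the article does not state. Main analyses gives no significance level, since 0.05 appears only in the Power calculation, and no section says that either outcome suffices. Under a both-must-succeed rule there is no inflation. That stands, and the figures here are therefore conditional.

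A second reply is that this is a condensed article, and an analysis plan not shown may settle the order or the allocation of alpha. That is fair as far as silence goes. But the article does state a multiplicity rule, and that rule stops short of the two primaries. It also commits the full 0.05 to HbA1c, so a later split of alpha would undercut the published sample size, as step 5 of the working shows. The choice is tied to the design.

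Three stronger readings are tempting but not supported:
- *A reader might infer an error close to 10 %.* That is the independence limit, and the article itself shows dependence because HbA1c is an input to UKPDS risk.
- *A reader might infer further inflation from testing 6 and 12 months separately.* Main analyses specifies one mixed model per outcome and no separate tests by visit.
- *A reader might infer that the missing power planning for UKPDS risk adds to the false-positive rate.* It affects the chance of missing a real effect, which is a different matter. Sizing a trial on one of two primaries is also common.

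**Conclusion.** The concern holds in conditional form. The plan has two unranked primary outcomes, no stated success rule and no error control across them, while the sample size spends all of alpha on HbA1c.

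If either outcome suffices and each is tested at 5 %, the family-wise error exceeds 5 % under every assumed correlation from 0 to 0.9. The ceiling is 9.75 %, and the ranges are about 7 to 9.7 % for overall group tests and 6.4 to 8.8 % for Sidak-corrected pairs. The correlation range is an assumption. The dependence between the outcomes works in both directions: it reduces the inflation, and it weakens a second positive result as confirmation.

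This should be corrected, but it does not invalidate the design.

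**What to change.** In Main analyses, state a fixed sequence that uses the planned group effect from whichever model is fitted (mixed ANCOVA or multi-level). Suggested wording: *The group effect on HbA1c is tested first at the 0.05 level. The group effect on UKPDS risk is tested confirmatorily at the 0.05 level only if the HbA1c test is significant; otherwise it is reported as supportive. Post hoc arm comparisons keep Sidak's correction within each outcome.*

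HbA1c goes first because the trial was sized on it. The change needs wording only: there are no more participants, and the power of the planned HbA1c test is untouched.

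The cost is that a positive result on UKPDS risk without one on HbA1c can no longer be a primary claim. The sequence protects the two group tests; arm-pair claims remain protected within each outcome, as now. The order should be fixed before allocation is revealed to the analyst.

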## Methods/Design

A three-arm randomised controlled trial (RCT). Eligible participants will be randomly allocated to either a group self-management intervention (SMI), SMI plus risk results (SMI + RR), or standard usual care. See Additional file 1 for the complete SPIRIT checklist.

### Setting

The study will be conducted in GP surgeries and community diabetes clinics within the National Institute for Health Research (NIHR) Eastern Clinical Research Network (CRN). To maximise patient participation in this study two models of recruitment and intervention delivery are proposed (i) standalone and (ii) hub and spoke. Standalone practices will recruit participants from their own patient lists and deliver the interventions in-house. In the hub and spoke model, one practice will act as the hub taking responsibility for recruitment and intervention delivery for smaller local spoke practices that identify eligible patients from their patient lists.

### Ethical approval and trial registration

Ethical approval for this study has been granted by the East of England Research Ethics Committee (ref 12/EE/0437). Local governance and assurances were issued by Norfolk and Suffolk Primary and Community Care Research Office, Cambridgeshire Community Services National Health Service (NHS) Trust, and Essex and Hertfordshire Comprehensive Local Research Network (CLRN) Office. A Data Monitoring Committee will be convened to review interim data and monitor safety and overall conduct of the trial. This study has been registered at ClinicalTrials.gov; registration identifier NCT01891786.

### Recruitment

#### Primary care providers

The Eastern CRN will recruit suitable primary care providers. Participating GP surgeries or community diabetes clinics must be research active and demonstrate adequate numbers of eligible patients. Recruiting staff will need to have received Good Clinical Practice (GCP) training. Practices will be offered CRN research nurse support where they do not have sufficient resources to complete all study activities.

#### Patients

Patients diagnosed with type 2 diabetes who are registered at a GP surgery within the East of England, and who are due an annual diabetes review within the recruitment window will be invited to participate. Eligible patients must be: aged between 25 and 74 years at the time of recruitment, of White, Afro-Caribbean or Asian-Indian ethnicity, be fluent in spoken English, and have had an HbA1c of ≥6.45 % (47 mmol/mol) in the 6 months preceding recruitment. Patients will be excluded if they have: history or diagnosis of ischaemic heart disease, transient ischaemic attack (TIA) or peripheral vascular disease, current serious or enduring mental health problems that would prevent study participation, are currently undergoing treatment for a life-threatening condition or are in the terminal stages of a condition. Participants who do not fit the ethnicity requirements will be excluded; this is because the genetic test and a primary outcome measure (UKPDS Risk Engine) have not been validated outside of the described ethnic groups. Adults who cannot consent for themselves will also be excluded.

Patients due their annual diabetes review within the 8-week recruitment window will be assessed for eligibility and invited to participate in the study via letter of invitation or opportunistically at the time of an appointment. Each practice will recruit between one and three cohorts of 15 participants.

Eligible interested patients will be invited to a consenting appointment where they will have the opportunity to review the participant information sheet with the practice or research nurse and give written informed consent to participate in the study. Once participants have completed baseline questionnaires they will be randomised to study condition, see Fig. 1.

